### Interim analyses {21b}

Not applicable; no interim analysis was performed.

### Methods for additional analyses (e.g., subgroup analyses) {20b}

The effects of the intervention on the primary and secondary outcomes will also be analyzed with additional per-protocol analysis with the participants who attended all 6 group meetings.

### Methods in analysis to handle protocol non-adherence and any statistical methods to handle missing data {20c}

Non-adherence will be handled with the use of the ITT principle in the analysis, by which we aim to avoid the effects of potential study dropouts and protocol deviations. The analysis will be made with the complete parts of the data for each statistical unit, and incomplete parts will be omitted. Missing data will be handled with suitable methods after evaluating the mechanism [73] under which the missing data occurs.

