### Sample size {14}

The total sample size of *n*=144 is based on the power calculation, when *α*=0.05, power=0.8, and effect size=0.5, and the estimated loss of participants is 15%. The calculation is based on the decline of 7 points assessed with the Center for Epidemiologic Studies Depression (CES-D) Scale.

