#### Implementation {16c}

The research dietitian will register eligible participants after obtaining consent at a face-to-face meeting. A data manager not connected to the study will perform the randomization and send the random numbers and group assignment directly to the research dietitian by email, who provides information about the allocation results to the participants by SMS and email including the meeting schedule and group program. If a person is unwilling to participate in the BGM control group after being randomized into it, she/he will be encouraged to participate by the research dietitian, highlighting that all participants in the BGM group will have an opportunity to participate in one Food for Mind nutrition meeting and receive the Food for Mind counseling material at the end of the study. Naturally, there is an option to refuse to participate in the study.

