## Statistical methods

### Statistical methods for primary and secondary outcomes {20a}

The effects of the intervention on the primary and secondary outcomes will be analyzed following the intention-to-treat (ITT) principle. Group differences will be estimated using linear mixed effects models which allow considering the nested dependency structure generated from small groups and small group counselors in the data. All tests will be conducted using an alpha level of 0.05 and reporting 95% confidence intervals. Statistical analysis will be performed using the R software [72] and IBM SPSS Statistics® (IBM Corp., Armonk, NY, USA).

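### The protocol foresees refusal on allocation to the control arm without providing for continued outcome collection, and leaves the missing-data method to a judgement that observed data cannot settle

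*Protocol article*

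**What the plan says.** Implementation {16c} deals with the person who objects to the control allocation: "If a person is unwilling to participate in the BGM control group after being randomized into it". The research dietitian encourages such a person to stay, pointing to the later Food for Mind (FM) session and material. The paragraph then closes: "Naturally, there is an option to refuse to participate in the study". It has no counterpart for FM. It does not say whether someone who declines the group is still asked for the 8-week, 6-month and 12-month questionnaires.

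The section on non-adherence and missing data {20c} does three things:

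- It presents ITT as the means by which the trial hopes to escape the consequences of dropout.
- It says "The analysis will be made with the complete parts of the data for each statistical unit, and incomplete parts will be omitted".
- It adds "Missing data will be handled with suitable methods after evaluating the mechanism".

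Statistical methods {20a} names linear mixed-effects models under ITT. The additional analyses {20b} name only a per-protocol analysis of those who attended all six meetings.

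**The concern.** The trial is open label and its primary outcome is self-reported CES-D change to 12 months. Participants learn their arm after consent and baseline, and recruitment presents the study as one about nutrition. Someone who wanted the nutrition group may leave on learning of the other allocation, and the protocol itself expects this in BGM. Retention may also differ for another reason. The research dietitian who runs the FM sessions also sends the follow-up reminders and collects the questionnaires, while BGM is led by an outside counselor.

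If such refusals are more common in one arm, and leavers would have fared differently from stayers, the 12-month comparison is biased. ITT settles the arm in which a person is counted. It does not create the outcome that was never collected.

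The rule for missing data does not close this gap. Observed data can cast doubt on missing completely at random. They cannot distinguish MAR from MNAR, and that is the distinction at issue when people leave because of their allocation. A method chosen after such an evaluation is data-dependent, and the premise behind the choice cannot be verified.

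**Working it through.** **Inputs from the protocol.** Sample size {14}: "The total sample size of *n*=144 is based on the power calculation", with "power=0.8, and effect size=0.5, and the estimated loss of participants is 15" per cent; and "The calculation is based on the decline of 7 points assessed with the Center for Epidemiologic Studies Depression (CES-D) Scale". Statistical methods {20a}: "All tests will be conducted using an alpha level of 0.05" (sidedness not stated; two-sided assumed). Allocation is 1:1, 72 per arm. The implied SD is 7/0.5 = 14; it is derived, not stated.

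**The plan's own figure.** For d = 0.5, two-sided 0.05 and power 0.80, n per arm = 2(1.960 + 0.842)²/0.5² ≈ 62.8, so 63, or 126 in total. Then 126 × 1.15 = 144.9, which agrees with 144 to within rounding. (Division by 0.85 would give 148.2. Nothing below depends on this.) The 15% is one overall figure and is not split by arm.

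**Bias formula.** Let D be the mean difference in 12-month CES-D change, leavers minus stayers, that remains after baseline adjustment. Take D as equal in both arms. Let c and f be the proportions lost in BGM and FM. Each arm's observed mean then misses its full-arm mean by loss × D, so

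bias in (FM − BGM) = (c − f) × D.

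D, c and f are assumptions. Total loss is held at 15%, so (c + f)/2 = 0.15, and D runs from 5 to 10 points.

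**Standard error.** SE = 14 × √[1/(72(1 − c)) + 1/(72(1 − f))]. This ignores group clustering and any precision gained from baseline.

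| BGM / FM loss | Bias (points) | Share of 7 points | SE | Type I error with no true effect |
|---|---|---|---|---|
| 15% / 15% | 0 | 0% | 2.5 | 0.05 |
| 20% / 10% | 0.5 to 1.0 | 7% to 14% | 2.5 | 0.054 to 0.068 |
| 25% / 5% | 1.0 to 2.0 | 14% to 29% | 2.5 | 0.068 to 0.123 |
| 30% / 0% | 1.5 to 3.0 | 21% to 43% | 2.6 | 0.090 to 0.215 |

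Example: (0.20 − 0.10) × 5 = 0.5 and (0.20 − 0.10) × 10 = 1.0. With 57.6 and 64.8 completers the SE is 14 × √(1/57.6 + 1/64.8) = 2.54, so the bias is about 0.2 to 0.4 standard errors.

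**Direction.** If leavers would have done worse (D > 0) and BGM loses more, the BGM mean looks too good and the FM advantage is understated. If leavers would have done better, it is overstated. The documents do not fix the sign.

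**Power.** Power is 0.789 with 61 completers in each arm and 0.777 with 72 and 50.4 (normal approximation). Uneven loss costs little precision. The issue is bias.

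**The case against.** A reader might infer more than the text supports, in four ways.

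- **That participants with gaps are deleted.** The sentence on omission speaks of the complete parts for each unit. Beside the mixed model in {20a}, it can be read as keeping every observed visit, which is valid under MAR. This objection stands. It helps little for someone who leaves at allocation, because that person contributes at most a baseline value and the 12-month contrast then rests on MAR.
- **That decliners get no follow-up.** The protocol does not say so. The option to refuse may only restate the general right to withdraw, and the SMS reminders in {18b} are not made conditional on attendance. What can be said is that {16c} does not provide for continued outcome collection.
- **That dropout will be one-sided.** This is not established. Either arm may withdraw, the Discussion says that group activities may be too demanding for some people with depression, and the 15% is overall.
- **That the method would be chosen with results in view.** Blinding {17a} plans re-coding by an unconnected data manager, or external analysis if possible. That reduces the risk, but it does not make the choice prespecified.

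It is also fair to say that a named MAR assumption and a delta-adjusted analysis are typical content of a statistical analysis plan, which may exist and is not shown. Their absence is not the point. The point is what {20c} does state: a data-dependent rule, and a reliance on ITT for something that ITT cannot do. An analysis plan that follows {20c} inherits both.

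Finally, the moderate illustrations are small beside a standard error of about 2.5 points. That is correct and limits the weight of the point.

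**Conclusion.** The concern holds in limited form. The protocol anticipates refusal triggered by the BGM allocation, does not provide for collecting outcomes afterwards, credits ITT with protection that it cannot give, and leaves the missing-data method to an evaluation that cannot separate MAR from MNAR. The 12-month CES-D contrast is exposed to bias if refusal differs by arm.

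The size and sign of that bias are unknown. The illustrative 0.5 to 1.0 points (7% to 14% of the 7-point target) rests on an assumed 20%/10% split and an assumed leaver–stayer difference of 5 to 10 points after baseline adjustment. With equal loss and an equal difference in both arms it is zero. The larger values in the table need more extreme splits. The documents do not support saying that usable data will be discarded, that decliners are barred from follow-up, or that loss will occur in BGM alone.

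The change should still be made. It is cheap, and outcomes that were never collected cannot be recovered at the analysis stage.

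**What to change.** 1. **Implementation {16c}.** Separate declining the group sessions from withdrawing from the study. Invite decliners in either arm to complete the scheduled 8-week, 6-month and 12-month questionnaires, and analyse them as randomised. The right to withdraw altogether is unchanged.
2. **Missing data {20c}.** Replace the choice made after evaluating the mechanism with a fixed primary analysis: a likelihood-based linear mixed model on all available visits of all randomised participants, under MAR. State that omission refers to unobserved visits and not to participants.
3. **Sensitivity.** Prespecify one delta-adjusted analysis in which the shift for missing 12-month CES-D values varies separately by arm, and report where the conclusion changes.
4. **Wording.** Drop the statement that ITT avoids the effects of dropout.

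The cost is revised wording, notice of the change to the ethics committee, a few extra questionnaires and one sensitivity analysis. Recruitment is already under way, so the follow-up change can help only participants who have not yet passed their 12-month visit. The analysis wording can still be fixed before outcome data are examined.

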### Plans to give access to the full protocol, participant level-data, and statistical code {31c}

The datasets analyzed during the current study are available from the corresponding author on reasonable request.

## Oversight and monitoring

### Composition of the coordinating center and trial steering committee {5d}

The Food for Mind study is considered a low-risk trial designed by an experienced multidisciplinary research team, under whose guidance the study will be managed without the need for a steering committee. The research dietitian and principal researcher are responsible for the trial’s day-to-day activities, while the recruitment process is carried out in collaboration with the staff of health care providers. The co-operating units are regularly informed about the recruitment process and future interventions. The research group plays a supporting role. The University of Eastern Finland provides organizational support, including statistical expertise. The ethics committee is informed about any possible changes in the study protocol.

### Composition of the data monitoring committee, its role, and reporting structure {21a}

This strength-based nutrition group intervention is founded on the “Food for Health” Finnish Nutrition and Food recommendations to improve diet quality without any risks to the adult study population. Therefore, establishing a data monitoring committee (DMC) was considered unnecessary

### Adverse event reporting and harms {22}

This is a low-risk trial, and adverse events and harms are not anticipated nor monitored. However, if psychological distress is noticed in relation to the group sessions, the participants are guided to discuss it in their treatment unit.

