**Methods:**

Participants (*N*=144, aged 20–65 years) with a diagnosis of moderate or severe depression recruited in collaboration with outpatient care units will be randomized into two arms: Food for Mind (FM) nutrition intervention (*n*=72) or Bring Good Mood (BGM) social support control group (*n*=72). Both arms will be provided with 6 group sessions over an 8-week period. FM involves improving diet quality by applying strength-based behavioral nutrition counseling and activities facilitated by a registered dietitian. The control arm comprises a befriending protocol. During the interventions, all participants will continue their treatment for depression as usual. Longitudinal data are collected at baseline, at 8 weeks, and at 6- and 12-month follow-ups. Depressive symptoms, diet quality, eating behavior, ability to work and function, and quality of life are assessed by self-reported questionnaires. A treatment expectancy questionnaire will be administered at baseline and an acceptability questionnaire at 8 weeks. The Center for Epidemiologic Studies Depression Scale is used as the primary endpoint at 1 year. The results will be analyzed with linear mixed-effects models. Economic evaluation includes both cost-effectiveness and cost-utility analysis. Two incremental cost-effectiveness ratios will be calculated to evaluate the incremental cost per QALY and the incremental cost per improvement in CES-D.

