### Eligibility criteria {10}

#### Inclusion criteria

Male and female participants will be eligible if they (1) are aged between 20 and 65 years, (2) have the ICD-10 diagnosis of depression (F32.1, F32.2, F32.8, F32.9, F33.1, F33.2, F33.8, F33.9, or F34.1), (3) have an individually tailored treatment and rehabilitation plan in an outpatient treatment unit, (4) are receiving treatment (medication and/or psychotherapy) that has remained unchanged for at least 2 weeks prior to randomization, and (5) are willing to participate in a group-based intervention for 8 weeks including 6 group sessions.

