#### Exclusion criteria

Participants will be excluded if they (1) have a medical illness that is clinically unstable and which could be aggravated by the intervention, (2) are pregnant, (3) are participating in another nutrition or exercise intervention, and (4) have a current depressive episode or recurrent depressive disorder that is severe with psychotic features, a personality disorder, a severe eating disorder, and/or a substance abuse disorder.

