The process of recruiting study participants for a randomized clinical trial has been found to be challenging in the population of individuals with depression [75], as was also found in a randomized controlled SMILES trial of dietary improvement for adults with major depression [28]. Group activities are increasingly used in the treatment of depression in health care but may be too demanding for some persons with depression. Therefore, the group sizes of this study are kept suitably small. In addition, the subjects’ thoughts about the suitability of the group intervention to them and their readiness about participating are discussed in the first meeting with the research dietitian. Further, the health care staff may be unfamiliar with nutrition care as part of the treatment of depression, and recruiting eligible patients for the study may require a particular interest in bringing up the topic of participation in the study. To facilitate the recruitment, we have produced material to be used in recruiting staff. Moreover, the randomization of participants to the intervention and control groups might discourage some patients from participating in the study, even though they will get an option to have social peer support in the control group, to take part in one nutrition meeting, and get all the printed material at the end of the study.

The course of research has been delayed for more than 6 months because of the global COVID-19 pandemic. The priority of outpatient care units has been on primary care, which has limited the time left for recruiting patients. In addition, national restrictions to group gatherings and the closure of research facilities due to the pandemic have caused an interruption to recruitment and running group sessions. The strengths of this study include the study design (RCT) and the recruitment of study participants in collaboration with outpatient care units confirming the participants’ depression diagnosis and ongoing treatments. Moreover, the study utilizes behavior change theories as applied in a strength-based counseling method to achieve improvement in diet quality, and the effect of social peer support is controlled with the “befriending” control group.

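### Harms are by decision not monitored, so the trial will have no by-arm count of serious events or individual deterioration, and its two statements about risk do not agree

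*Protocol article*

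**What the plan says.** Under Adverse event reporting and harms {22}, the protocol article states: "This is a low-risk trial, and adverse events and harms are not anticipated nor monitored". Its only provision is that "if psychological distress is noticed in relation to the group sessions, the participants are guided to discuss it in their treatment unit". Nothing there says that such distress is recorded, counted or compared between arms.

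Under Composition of the data monitoring committee {21a}, the intervention is said to follow national nutrition recommendations "to improve diet quality without any risks to the adult study population". The conclusion drawn is: "Therefore, establishing a data monitoring committee (DMC) was considered unnecessary". The section on the coordinating centre and steering committee {5d} uses the weaker description, that the trial is low in risk.

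The abstract describes participants "with a diagnosis of moderate or severe depression recruited in collaboration with outpatient care units". The inclusion criteria list the codes "F32.1, F32.2, F32.8, F32.9, F33.1, F33.2, F33.8, F33.9, or F34.1", which contain the severe episodes F32.2 and F33.2.

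Table 2 schedules CES-D, TFEQ-R18, ecSI 2.0, medication and body composition at baseline, 8 weeks, 6 months and 12 months. The Primary outcomes section defines clinically relevant change only in the direction of improvement: a fall of at least 50%, or a score below 12, 16 or 22. The Economic evaluation section says that data on the use of health care services are not available. Dissemination plans {31a} foresee release of the model through national platforms after the study.

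**The concern.** The decision not to monitor harms is stated outright, so it cannot be read as a detail that the article leaves to a fuller protocol or an analysis plan. Followed as written, the trial ends with no count, in either arm, of deaths, hospital admissions or self-harm over 12 months, in a population that includes people with severe depressive episodes. It also has no definition of individual worsening on its own primary scale.

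The model is meant for routine use. A health care provider asking how often participants had a serious event, or became clearly worse, in either arm would get no answer. The economic data cannot fill the gap, because service use is not collected for that analysis.

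The wording about risk is also inconsistent. No risk at all, low risk, and a provision for distress in the sentence after harms are said not to be anticipated cannot all describe the same trial.

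**Working it through.** The plan gives no figure for harms, so there is none to reproduce. The check has three parts.

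**1. The passages side by side**

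| Place | Position on risk |
|---|---|
| Data monitoring committee {21a} | No risks to the study population |
| Coordinating centre {5d} | Low risk |
| Harms {22}, first sentence | Low risk; harms neither expected nor monitored |
| Harms {22}, second sentence | Distress around sessions is possible and leads to referral |

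The first row is stronger than the other three.

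**2. What the planned data can and cannot show**

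- Mean worsening of mood: visible. CES-D change is the primary outcome, with 8-week and 6-month changes as follow-up outcomes, compared between arms by mixed models.
- Mean worsening of eating behaviour, weight or BMI: visible. All are pre-specified outcomes at the same visits.
- Individual worsening on CES-D: the data are collected, but no analysis is stated.
- Serious events: not collected.

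A mean can hide individual worsening. Sample size {14} gives a 7-point decline and an effect size of 0.5. If the two figures correspond, SD = 7/0.5 = 14. The SD of individual change is not given. Assume normal changes and a baseline-to-follow-up correlation r, so that SD of change = 14 × √(2(1 − r)):

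- r = 0.50: SD = 14.0. In an arm with a mean fall of 7, the share with any rise is P(Z > 7/14.0) = P(Z > 0.50) = 31%.
- r = 0.75: SD = 9.9. The share is P(Z > 7/9.9) = P(Z > 0.71) = 24%.

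By symmetry, the same 24% to 31% would show a rise of 7 points or more in an arm with no mean change. A 7-point rise therefore cannot serve by itself as a marker of harm, and a by-arm comparison is needed to interpret any count.

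**3. What recording serious events would buy**

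Inputs: 72 per arm (Sequence generation {16a}); 15% loss (Sample size {14}), so 72 × 0.85 = 61.2, taken as 61. With zero events in n people, the exact one-sided 95% upper bound is 1 − 0.05^(1/n).

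- n = 72: 1 − 0.05^(1/72) = 4.1% (rule of three: 3/72 = 4.2%).
- n = 61: 1 − 0.05^(1/61) = 4.8%.
- If recording covered only half the arm (36, an assumption for illustration): 1 − 0.05^(1/36) = 8.0%.

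The chance of seeing at least one event is 1 − (1 − p)^n. For assumed true risks p:

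| p | n = 72 | n = 61 |
|---|---|---|
| 1% | 0.52 | 0.46 |
| 2% | 0.77 | 0.71 |
| 5% | 0.98 | 0.96 |

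Without recording there is no numerator, and no bound can be given.

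**The case against.** The case for leaving the plan as it is has substance. The intervention is dietary counselling in line with national recommendations. Every participant has a treatment plan in an outpatient unit and usual care continues, so events can be dealt with clinically there. Acceptability at 8 weeks includes perceived burden. The primary estimate and its inference do not depend on harm recording. All of this stands, and it limits the weight of the point. It does not supply a count of events by arm.

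Several stronger readings are tempting, and the documents do not support them:

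- **That the exclusion criteria concede harm to participants.** The criterion excludes people who "have a medical illness that is clinically unstable and which could be aggravated by the intervention". It concerns unstable medical illness in people who are not enrolled, and does not say that depression is the illness meant. Screening out vulnerable people fits a claim of low risk in those who remain.
- **That the Discussion admits harm.** The remark that group activities "may be too demanding for some persons with depression" belongs to a paragraph on recruitment. It is followed by mitigation: small groups, and a talk about suitability and readiness at the first meeting.
- **That the trial sets out to show there are no risks.** That phrase is the premise for having no data monitoring committee. It is neither an objective nor a planned conclusion, and implementation is tied to cost-effectiveness and acceptability.
- **That the trial would not notice if the intervention worsened mood or eating.** Average worsening relative to control would appear in the planned comparisons.
- **That all participants have moderate or severe depression.** The abstract says so, but the codes also admit other, unspecified and F34.1 diagnoses.

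There are also fair objections to any remedy. Recruitment began on 1 February 2018, so coverage would be partial. The research dietitian leads the intervention groups, collects the questionnaires and is not blinded, so ascertainment could differ by arm.

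**Conclusion.** The point holds in a limited form. By stated decision, the trial will have no by-arm count of serious events and no planned account of individual deterioration, in outpatients with depression that includes severe episodes and for a model intended for routine care. The risk wording in {21a} is stronger than that in {5d} and {22} and must be reconciled with it.

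The size is modest. Full recording with no events would bound the risk at about 4.1% (72 followed) or 4.8% (61 followed), and less tightly with partial coverage. These bounds assume independent participants and complete reporting among those followed. The trial is too small to rule out rare harms, but a weak bound is more than none.

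The absence of a data monitoring committee is not itself the fault, and nothing here shows that enrolled participants are at risk. The primary analysis is unaffected.

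**What to change.** 1. Replace the sentence in {22} that says harms are not monitored. At the remaining 8-week, 6-month and 12-month contacts, put one identical self-report item to both arms on hospital admission and self-harm since the previous contact. Log deaths in the same way in both arms as they become known, since self-report cannot capture them.
2. State that participants already past a contact are not covered for it, and that ascertainment is unblinded. Give the number covered per arm as the denominator.
3. From CES-D data already collected, report by arm the distribution of individual change, including the number who worsened from baseline. Fix any margin before the arms are compared. If 7 points is shown, do not present it as a validated harm threshold: in {14} it is the decline behind the sample size. Show the already planned weight and BMI change in the same table.
4. Bring the wording in {21a} into line with {5d} and {22}.

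The cost is one questionnaire item, one table and a notice to the ethics committee, which the protocol already requires for changes. Some work falls on a research dietitian with limited resources. The care of participants in distress stays as written.
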